### Statistical Analysis Plan

#### Overview

We will use SAS 9.2 (SAS Institute, Inc) to calculate frequencies and percentages for categorical factors and means with standard deviations and/or percentiles for continuous factors. Pearson’s chi-square tests will be used for primary outcome (number of quality indicators met in HealthPROMISE vs control arm) and secondary outcomes. We will calculate percentage score for each patient at baseline and at week 104 ([number of quality metrics met/quality metrics eligible]*100). Change in the percentage score from baseline to week 104 will be aggregated for each arm to calculate percentage-point improvement in quality metric, similar to the strategy by Cebul et al [26].

Analysis of covariance (ANCOVA) will be performed to assess differences in the area under the curve of QOL scores while adjusting for baseline QOL score. To assess the association between patient and practice characteristics and achievement of eligible quality metrics, we will use multivariable analyses. Since the data will be hierarchically structured, with patients clustered within physicians and metrics clustered within patients, we will construct multilevel, generalized, linear mixed models with random effects to determine predictors of quality care, similar to the strategy used by Kanwal et al [27]. Independent variables will include demographic characteristics (age, gender), education and income level, race and ethnicity, computer usage, eHealth literacy scores, clinical characteristics (comorbidities, phenotype, disease severity), and provider characteristics (gender, age, site of practice, years of practice, presence of nurse practitioner).

#### Interim Analysis

Interim analysis will be performed once 150 patients are followed up for week 52. If primary outcome is met by that time, all patients will be offered HealthPROMISE app and followed for the additional 52 weeks.

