#### Disease Specific Quality of Life Questionnaire

The Short Inflammatory Bowel Disease Questionnaire (SIBDQ) [20] is a validated and reliable tool to measure health-related QOL in adult patients with IBD. The questionnaire consists of 10 questions scored in four domains: bowel symptoms, emotional health, systemic systems, and social function. The SIBDQ is a respected QOL questionnaire used extensively in academic research and clinical trials. Study patients in the control arm and interventional arm will complete an SIBDQ as part of a survey to objectively measure QOL at baseline and at exit (52 weeks or 104 weeks). Additionally, patients in the intervention arm will be asked to complete the SIBDQ every 2 weeks; this will be used to classify patients as having “good control,” “fair control,” or “poor control.”

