**Outcome**			
	Improvement in quality of care metrics	Provider, Center	Quarterly reports
	Improvement in quality of life	Provider, Center	Quarterly reports
	Readmission rate in two arms	Provider, Center	Quarterly reports

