#### Sample Size Justification

Study endpoints will be primarily assessed using intention-to-treat (ITT) analysis; however, per-protocol analysis will also be performed. The study is to be powered such that there is a>80% probability of demonstrating a difference with a *P* value *(P* = .05) using a two-tailed *t* test.

We assume that 128 out of 150 subjects (85%) in the intervention arm will meet all quality indicators (primary outcome) and expect that this percentage will be at least 15% lower in the control arm. A sample size of 95 patients will be needed in each arm to achieve at least 80% power to detect the difference with a 5% one-sided significance level.

Accounting for an estimated 30% attrition rate, we will require a total of 250 IBD patients to be enrolled in the study. Since some patients may agree to enroll but not download the app or use the PIN, we will recruit a total of 300 patients in the study.

For secondary outcomes related to QOL, the control arm is not a placebo arm and physicians are free to initiate any therapy based on patients' symptoms. Hence, we will assess the difference in proportion of patients achieving MCID in the HealthPROMISE arm versus control arm in the study. Using the distribution-based approach, an effect size of 0.5 SD is the closest estimate for determining MCID for SIBDQ and EQ-5D. Assuming that 20% more patients in HealthPROMISE arm will achieve MCID than in the control arm, the sample size of 250 patients will have 88% power to detect the difference with a 5% one-sided significance level and an estimated 30% attrition rate.

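### The week-52 interim rule can end the comparison that the week-104 primary analysis needs, and neither the interim measure nor its significance level is stated

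*Protocol article*

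**What the plan says.** All places are in the protocol article.

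- **Interim Analysis:** "Interim analysis will be performed once 150 patients are followed up for week 52". The consequence follows: "If primary outcome is met by that time, all patients will be offered HealthPROMISE app and followed for the additional 52 weeks". The section does not say what counts as the outcome being met, and gives no significance level.
- **Statistical Analysis Plan, Overview:** "We will calculate percentage score for each patient at baseline and at week 104", and "Change in the percentage score from baseline to week 104 will be aggregated for each arm". The test is named as well: "chi-square tests will be used for primary outcome (number of quality indicators met in HealthPROMISE vs control arm) and secondary outcomes". No week-52 score is defined for the primary outcome.
- **Sample Size Justification:** the size per arm is chosen for "at least 80% power to detect the difference with a 5% one-sided significance level". A general statement in the same section gives a two-tailed test at 5%. These are the only significance levels in the article.
- **Disease Specific Quality of Life Questionnaire:** the SIBDQ is completed "at baseline and at exit (52 weeks or 104 weeks"), so two exit times are named there without a rule linking them to the interim.
- **Discussion, Principal Findings:** the hypothesis concerns the end of a 2-year period, against control patients using the education app alone.

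**The concern.** The interim rule acts on the primary outcome at a time for which that outcome has no definition. Its action falls in exactly the 52 weeks that lead up to the planned primary measurement. If it triggers, control patients may use the intervention during the second year, and the two-year comparison with the education app alone is no longer available free of crossover.

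A second issue is error control. The interim is an additional occasion on which the trial can declare success, and nothing in the article says how the 5% is shared between the two looks.

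**Working it through.** **1. The plan's own sample size.** Inputs from Sample Size Justification: 85% versus 70%, one-sided 5%, 80% power. Pooled formula without continuity correction, mean proportion 0.775:

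n = [1.645 × √(2 × 0.775 × 0.225) + 0.842 × √(0.85 × 0.15 + 0.70 × 0.30)]² / 0.15² = (0.971 + 0.489)² / 0.0225 ≈ 94.8, so 95 per arm.

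The stated 95 is reproduced with the full 5% in a single analysis.

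**2. Timing of a trigger.** Table 1 plans 300 patients in 6 months. Even accrual (assumed) is 50 per month.

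- No attrition: the 150th patient enrols at month 3 and reaches week 52 at about month 15.
- 30% attrition, assumed complete by week 52: 150 / 0.70 ≈ 214 must be enrolled, at month 214 / 50 ≈ 4.3, so the look falls at about month 16.3.
- The first patient reaches week 104 at about month 24.

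Either way the trigger precedes every week-104 assessment. For the look to slip to month 24, the 150th patient would have to enrol at month 12. That is 150 / 12 = 12.5 per month, a quarter of the planned rate (no attrition).

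Patients not yet at week 52 at the look number 300 − 150 = 150 without attrition, or 300 − 214 = 86 with it. They span both arms, so about 75 or 43 are controls.

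**3. Probability of a trigger under the design assumptions.** With 75 per arm and 85% versus 70% assumed to hold already at week 52:

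power = Φ{[0.15 × √75 − z × √(2 × 0.775 × 0.225)] / √(0.85 × 0.15 + 0.70 × 0.30)}

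- One-sided 5% (z = 1.645): Φ[(1.299 − 0.971) / 0.581] = 71%.
- Two-sided 5% (z = 1.960): Φ[(1.299 − 1.157) / 0.581] = 60%.

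**4. Overall type I error if 5% is used at both looks.** This is the probability that either of two standard normal statistics crosses the 5% critical value. Their correlation is ρ × √t, where t = 150 / final N and ρ is the correlation between a patient's week-52 and week-104 outcomes. The article does not give ρ, so a range is shown. Final N is 300, or 210 after 30% attrition.

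| Final N | t | ρ | Two-sided | One-sided |
|---|---|---|---|---|
| 300 | 0.50 | 1 | 8.3% | 8.0% |
| 300 | 0.50 | 0.8 | 8.9% | 8.6% |
| 300 | 0.50 | 0.5 | 9.4% | 9.2% |
| 210 | 0.71 | 1 | 7.5% | 7.2% |
| 210 | 0.71 | 0.5 | 9.3% | 9.0% |

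**The case against.** **The interim level may be set elsewhere.** The article gives no interim threshold, so it does not say that 5% is used there. A condensed article may leave the boundary to a full protocol or analysis plan. This stands: a reader might infer that the trial's type I error is 7-9%, but the documents support that only conditionally. Nor does the match to 95 per arm prove that no boundary was intended, since a final one-sided level of 0.0467 would need only 98 per arm, and 300 recruited with 30% attrition leaves 105. The time-point conflict does not depend on any of this, because even a strict boundary, once crossed, leads to the same loss at week 104.

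**An efficacy trigger normally ends the clean comparison, and the randomised arms remain.** This also stands in part. A reader might infer that week 104 would compare app with app. The documents do not support that: the app is only offered, the sample-size section expects some patients never to download it, and the primary approach is intention-to-treat. What remains is early versus delayed access. That is a valid randomised contrast, but not the one the Discussion states. The two SIBDQ exit times suggest that two paths were foreseen, but no section says which comparison is confirmatory on each.

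**Quarterly reporting.** A reader might treat the Table 1 row "Readmission rate in two arms" as a further efficacy look. Readmission is not the primary outcome or a listed endpoint, and the table tracks progress, so it adds nothing to the error calculation.

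**Conclusion.** The point holds. As written, the Interim Analysis, the Overview and the hypothesis in the Discussion do not fit together. A trigger acts on a week-52 primary outcome that is not defined, and it comes about 24 − 15 = 9 months before any control could contribute a week-104 result on the education app alone (about 8 months with 30% attrition). The loss occurs only if the rule triggers, but that is the likelier path under the design assumptions: about 71% or 60%, if the 85% versus 70% difference is present by week 52 and the look is judged at 5%.

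The type I part is conditional. If the only stated level is used at both looks, the overall error is about 7-8% with perfectly correlated outcomes and up to about 9.4% at a correlation of 0.5, which is an assumption. A stricter interim level in an unseen document would reduce or remove this excess, but would not settle the time-point conflict.

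**What to change.** 1. **Define the interim measure.** State the week-52 form of the primary outcome and what result counts as met.
2. **State an interim efficacy level** that holds the overall 5% for the chosen sidedness and the actual information fraction. Examples are a Lan-DeMets O'Brien-Fleming-type boundary (about 0.003 then 0.049, two-sided, at half information) or Haybittle-Peto at 0.001. The first pair assumes the same outcome at both looks. If the looks use weeks 52 and 104, the correlation is lower and the error is bounded only by 0.003 + 0.049 = 0.052, whereas 0.001 with 0.049 sums to 0.050 and holds for any correlation.
3. **Reconcile the three sections.** If the rule triggers, the confirmatory comparison is the randomised week-52 one, and later data are reported as early-versus-delayed-access extension data. If it does not trigger, week 104 remains primary. State which patients enter the week-52 comparison, since 86 to 150 of those randomised would not yet have reached week 52.

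The cost is a paragraph of protocol text, a stricter interim threshold (so a lower trigger probability than in the working) and a slightly smaller final alpha. In sample size, a final one-sided level of 0.049 needs 96 per arm instead of 95, within the 300 × 0.70 / 2 = 105 expected. Making week 52 primary on both paths would be simpler, but it would give up the stated two-year hypothesis, so it is a trade-off for the sponsor and not needed here.

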#### Sample Size Justification

Study endpoints will be primarily assessed using intention-to-treat (ITT) analysis; however, per-protocol analysis will also be performed. The study is to be powered such that there is a>80% probability of demonstrating a difference with a *P* value *(P* = .05) using a two-tailed *t* test.

We assume that 128 out of 150 subjects (85%) in the intervention arm will meet all quality indicators (primary outcome) and expect that this percentage will be at least 15% lower in the control arm. A sample size of 95 patients will be needed in each arm to achieve at least 80% power to detect the difference with a 5% one-sided significance level.

Accounting for an estimated 30% attrition rate, we will require a total of 250 IBD patients to be enrolled in the study. Since some patients may agree to enroll but not download the app or use the PIN, we will recruit a total of 300 patients in the study.

For secondary outcomes related to QOL, the control arm is not a placebo arm and physicians are free to initiate any therapy based on patients' symptoms. Hence, we will assess the difference in proportion of patients achieving MCID in the HealthPROMISE arm versus control arm in the study. Using the distribution-based approach, an effect size of 0.5 SD is the closest estimate for determining MCID for SIBDQ and EQ-5D. Assuming that 20% more patients in HealthPROMISE arm will achieve MCID than in the control arm, the sample size of 250 patients will have 88% power to detect the difference with a 5% one-sided significance level and an estimated 30% attrition rate.

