**Results:**

Enrollment in the trial will be starting in first quarter of 2015. It is intended that up to 300 patients with IBD will be recruited into the study (with 1:1 allocation ratio). The primary endpoint is number of quality indicators met in HealthPROMISE versus control arm. Secondary endpoints include decrease in number of emergency visits due to IBD, decrease in number of hospitalization due to IBD, change in generic QOL score from baseline, proportion of patients in each group who meet all eligible outpatient quality metrics, and proportion of patients in disease control in each group. In addition, we plan to conduct protocol analysis of intervention patients with adequate HealthPROMISE utilization (more than 6 log-ins with data entry from week 0 through week 52) achieving above mentioned primary and secondary endpoints.

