## Methods

### Study Design

This is a phase III, single-center, pragmatic randomized controlled trial (RCT) to evaluate if a patient-centric self-monitoring and collaborative decision support platform will lead to sustainable improvement in overall QOL for IBD patients. It is intended that 300 patients with IBD will be recruited into the study (allocation ratio 1:1; Figure 4). After meeting all the inclusion criteria with no exclusions, patient is asked to complete a tablet-based screening questionnaire at the end of which patient is randomized at the point of care to intervention or control arm. Patients in the control arm will receive an IBD education app PIN whereas the intervention arm will receive HealthPROMISE app PIN (Figure 3). Intervention patients enter their data once every 2 weeks and this data is then made visible to providers using a Web-based dashboard integrated with the EHR (Figures 4 and 5). Intervention and control apps will be provided free of charge to patients, and patients will be given $25 after completing initial and end of study questionnaires.

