## Results

### Outcome Measures

All outcome data (Textbox 1) will be collected online. Additionally, we will conduct subgroup analysis of patients with poor disease control at week 0 (SIBDQ≤30) and in those with high patient-reported anxiety, depression, or stress achieving primary and secondary endpoints. We will assess change in inflammatory markers, endoscopic scores, and additional quality metrics in each group and determine predictors of HealthPROMISE and control app utilization and its impact on other primary and secondary end-points. Consistent with the pragmatic nature of the trial, study progress will be assessed throughout and effort will be optimized to better engage providers and patients (Table 1).

Primary and secondary endpoints.Primary endpointNumber of quality indicators met in HealthPROMISE versus control armSecondary endpoints
_Decrease in number of emergency visits due to IBD_

_Decrease in number of hospitalization due to IBD_

_Change in generic QOL score (EQ-5D) from baseline_

_Proportion of patients in each group who meet all eligible outpatient quality metrics_

_Proportion of patients in disease control in each group_

_Emergency visits in each group_

_Hospitalizations in each group_

_General QOL scores in each group_

_Per protocol analysis of intervention patients with adequate HealthPROMISE use (more than 6 log-ins with data entry from week 0 through week 52) achieving above mentioned primary and secondary endpoints_

**Table 1 table1:** Evaluation metrics for HealthPROMISE progress

Metric		Target Group	Goal / Timeline

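### Two competing primary endpoints: the trial is sized on patients meeting all indicators, the endpoint list names the number met, and power for the number is undetermined

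*Protocol article*

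**What the plan says.** The protocol article describes the primary endpoint in several places.

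- **Abstract, Results:** "The primary endpoint is number of quality indicators met in HealthPROMISE versus control arm". Outcome Measures (Textbox 1) repeats this.
- **Secondary endpoints, in the abstract and in Textbox 1:** "Proportion of patients in each group who meet all eligible outpatient quality metrics".
- **Statistical Analysis Plan, Overview:** "Pearson’s chi-square tests will be used for primary outcome (number of quality indicators met in HealthPROMISE vs control arm) and secondary outcomes". The same paragraph defines a patient-level percentage score (metrics met divided by metrics eligible, times 100) and adds: "Change in the percentage score from baseline to week 104 will be aggregated for each arm". It does not call that score the primary analysis variable.
- **Sample Size Justification:** "We assume that 128 out of 150 subjects (85%) in the intervention arm will meet all quality indicators (primary outcome". The control rate is put at least 15% below this, and 95 per arm is derived for 80% power at one-sided 5%. The paragraph before it promises a two-tailed t test at P = .05.
- **Interim Analysis:** if the primary outcome has been met once 150 patients have reached week 52, everyone is offered the HealthPROMISE app.

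**The concern.** The same all-or-none endpoint is secondary in the endpoint lists and primary in the sample size. The number of indicators met is primary in three places but has no effect assumption anywhere.

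The two endpoints can give different answers on the same data. Patients may gain several indicators and still miss one, which raises the number met and leaves the all-met proportion unchanged. If the choice stays open until results are seen, it can be made in favour of the better result.

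The named tests do not settle the matter. A Pearson chi-square test suits the yes/no endpoint but is assigned to the number met. A t test suits a score but stands beside a proportion calculation. The interim rule ends the randomized contrast when the primary outcome is met, and the article does not determine which outcome that is.

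**Working it through.** **Step 1. Reproduce the plan's figure.** Inputs from Sample Size Justification: p1 = 0.85; p2 = 0.85 − 0.15 = 0.70 (15% read as percentage points); one-sided 5% (z = 1.645); 80% power (z = 0.842). The mean proportion is 0.775.

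n per arm = [1.645·√(2·0.775·0.225) + 0.842·√(0.85·0.15 + 0.70·0.30)]² / 0.15² = 94.8, rounded up to 95.

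Power at 95 per arm is 0.801. The stated figure is a two-proportion calculation for the all-met endpoint.

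**Step 2. The same endpoint under the two-tailed test.** With z = 1.96 in place of 1.645, n = 121 per arm.

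| Evaluable per arm | Source | Two-sided power, 85% v 70% |
|---|---|---|
| 87 | 250 × 0.70 = 175 in total | 0.66 |
| 95 | stated requirement | 0.70 |
| 105 | 300 × 0.70 = 210 in total | 0.74 |

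The article adds 50 patients to the 250 to cover people who enrol but never download the app or use the PIN. Using 105 per arm assumes that none of that reserve is lost beyond the 30% attrition.

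**Step 3. The number or percentage score.** No mean difference or SD is given, so only a detectable standardized difference can be computed: d = (1.96 + 0.842)·√(2/n), two-sided 5%, 80% power.

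- n = 87: d = 0.42 SD
- n = 95: d = 0.41 SD
- n = 105: d = 0.39 SD

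**Step 4. Range of power for the score.** The differences and SDs here are assumptions, not figures from the article (95 per arm, two-sided 5%).

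| Difference in score (points) | SD 20 | SD 30 | SD 40 |
|---|---|---|---|
| 5 | 0.41 | 0.21 | 0.14 |
| 10 | 0.93 | 0.63 | 0.41 |
| 15 | >0.99 | 0.93 | 0.73 |

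**Step 5. Does 85% v 70% all-met imply a weak effect on the score?** Assume k independent indicators per patient, each met with probability p^(1/k).

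- k = 5: 96.8% v 93.1%, a difference of 3.7 points with SD about 9.8, so 0.38 SD.
- k = 10: 98.4% v 96.5%, a difference of 1.9 points with SD about 5.0, so 0.38 SD.

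At 95 per arm this gives power of about 0.83 one-sided and 0.74 two-sided, close to the all-met figures of 0.80 and 0.70. Independence is itself an assumption.

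**The case against.** The best defence is that this is a slip in labelling. Sample Size Justification calls the all-met proportion primary, and the chi-square test in the Overview fits that proportion, so the authors may have meant it throughout. That has force. It is why the finding is two competing primary endpoints, and not simply a power claim attached to a secondary one. It does not remove the contradiction, because the abstract, Textbox 1 and the Overview all say otherwise. Nor does condensation into an article explain it: these are incompatible statements, not omitted detail.

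A reader might infer more than the article supports in three ways.

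- **That the trial is underpowered for the number of indicators met.** Steps 4 and 5 show that power could lie on either side of 80%. The 1.9 to 3.7 points in step 5 look small, but they come with a small SD and amount to about 0.38 SD, close to the 0.39 SD detectable at 105 per arm.
- **That there are three incompatible primaries.** The percentage score is the number met rescaled by the number eligible, and it is never labelled primary. The firm contradiction is between number met and all met.
- **That no hypothesis covers quality of care.** Study Design does say the platform "will lead to sustainable improvement in overall QOL for IBD patients", as do the abstract's Objective and the end of the Introduction. But the outcomes listed in that Objective begin with quality of care, and Principal Findings states a hypothesis covering quality of care, QOL and resource use. This is a minor inconsistency in wording.

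**Conclusion.** The concern holds in this form: the article names two different primary endpoints, and its 95 per arm and 80% power apply only to the all-met proportion, at 85% v 70% and one-sided 5%. Under the two-tailed test that the same section names, that proportion has about 70% power at 95 per arm and 74% at 105.

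For the number met or the percentage score, power cannot be stated. Over assumed differences of 5 to 15 points and SDs of 20 to 40, it runs from 0.14 to above 0.99 (two-sided, 95 per arm). That range shows a missing basis and not a demonstrated shortfall. The mismatch itself rests on the text alone and needs none of these assumptions. It should be resolved before the interim analysis, because the interim rule depends on the primary outcome.

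**What to change.** Name one primary endpoint and make the abstract, Outcome Measures, the Overview, Interim Analysis and Sample Size Justification agree on it. Either option resolves the contradiction.

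- **(a) Percentage score.** Make the patient-level score at one fixed time point primary, compared between arms with baseline adjustment. Remove the primary label from the all-met proportion in Sample Size Justification and keep that proportion as secondary. Replace the chi-square test for the primary analysis. Restate power as a detectable difference at two-sided 5% and 80% power: about 0.39 SD with 105 evaluable per arm if 30% attrition applies to all 300, or about 0.42 SD with 87 per arm if it applies to 250. State an assumed SD so that the difference can be read in points.
- **(b) All-met proportion.** Make it primary in the abstract, Outcome Measures and the Overview, and keep the chi-square test. Restate its power under the two-tailed test: about 70% at 95 per arm, 74% at 105.

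Under either option, say which endpoint the interim rule refers to. As a minor point, align the QOL-only hypothesis in the abstract, Introduction and Study Design with the broader one in Principal Findings.

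The cost is wording and a recalculated power statement; making the texts agree needs no extra patients or data. The price of (a) is giving up the only effect assumption in the article, so adequacy then depends on the SD assumed. The price of (b) is that the stated 80% no longer stands at the planned size; 80% two-sided would need 121 evaluable per arm.

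### The plan promises more than 80% power for a two-tailed test at P = .05 but sizes the trial at a one-sided 5% level; 95 evaluable patients per arm give about 70% power two-sided

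*Protocol article*

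**What the plan says.** All the conflicting statements on level are in the Sample Size Justification of the protocol article.

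- The opening paragraph gives the general rule: "The study is to be powered such that there is a>80% probability of demonstrating a difference" at P = .05, "using a two-tailed" t test.
- The second paragraph sizes the primary outcome. For the intervention arm: "We assume that 128 out of 150 subjects (85%) in the intervention arm will meet all quality indicators (primary outcome"). For the control arm the authors "expect that this percentage will be at least 15% lower in the control arm". The result is: "A sample size of 95 patients will be needed in each arm", for "at least 80% power to detect the difference with a 5% one-sided significance level".
- The third paragraph allows for 30% attrition, asks for 250 enrolled, and raises recruitment to 300 because some patients may enrol without downloading the app or using the PIN.
- The last paragraph says of the QOL responder comparison that the "sample size of 250 patients will have 88% power to detect the difference with a 5% one-sided significance level", again with 30% attrition. It assumes a 20-point difference and gives no control rate.

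The Overview of the Statistical Analysis Plan says that Pearson's "chi-square tests will be used for primary outcome" and for secondary outcomes. It mentions no one-sided analysis.

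**The concern.** A one-sided 5% level is the same threshold as a two-sided 10% level when the effect is in the favoured direction. It needs fewer patients than the two-tailed 5% test promised at the start of the section. The article gives no reason for a one-sided test and does not say which statement governs. The chi-square test, as ordinarily run, is non-directional, so it fits the two-tailed sentence and not the basis on which 95 was obtained.

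The stake is the planning power. If the analysis is two-sided, the promised power is not delivered at the calculated sample size, nor at the recruitment target after the plan's own attrition. A reader who relies on the opening sentence would take the trial to be better powered than it is.

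**Working it through.** **Inputs.** Intervention rate p1 = 0.85 and control rate p2 = 0.70 (15 points lower), 95 per arm, 30% attrition, enrolment of 250 or 300, all from the Sample Size Justification. Allocation is 1:1 (Study Design).

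**Formula.** Two proportions, pooled variance under the null, no continuity correction:

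n per arm = [z_α·√(2p̄(1−p̄)) + z_β·√(p1(1−p1) + p2(1−p2))]² / (p1 − p2)²

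Here p̄ = 0.775, √(2 × 0.775 × 0.225) = 0.5906, √(0.1275 + 0.21) = 0.5809, and z_β = 0.8416 for 80% power.

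**Reproducing the plan's figure (one-sided 5%, z_α = 1.645).** (1.645 × 0.5906 + 0.8416 × 0.5809)² / 0.0225 = 94.8, so 95 per arm. This is the stated figure. Reading the 15% as a relative reduction (control rate 72.25%) gives 127, so the plan means 15 percentage points.

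**Same inputs at two-sided 5% (z_α = 1.960).** (1.960 × 0.5906 + 0.8416 × 0.5809)² / 0.0225 = 120.5, so 121 per arm. Other standard versions give 118 (unpooled), 119 (arcsine) and 134 (continuity-corrected). None gives 95, so that figure rests on the one-sided level.

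**Power.** Power = Φ{[√n × 0.15 − z_α × 0.5906] / 0.5809}. At n = 95, √95 × 0.15 = 1.462:

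- one-sided: Φ(0.845) = 80.1%
- two-sided: Φ(0.524) = 70.0%; exact binomial enumeration of the uncorrected chi-square test gives 70.7%

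| Evaluable per arm | How it arises | One-sided 5% | Two-sided 5% |
|---|---|---|---|
| 87.5 | 250 × 0.70 / 2 | 77.1% | 66.4% |
| 95 | stated requirement | 80.1% | 70.0% |
| 105 | 300 × 0.70 / 2 | 83.5% | 74.3% |
| 121 | needed for 80% two-sided | 87.9% | 80.2% |
| 125 | 250, no loss | 88.8% | 81.4% |
| 150 | 300, no loss | 93.2% | 87.9% |

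With 300 enrolled, 121 per arm means retaining 121/150 = 80.7%, that is, losing no more than about 19%. With 105 per arm, 80% two-sided power is reached at a control rate of 68.8%, a difference of 16.2 points.

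**QOL outcome.** 250 less 30% is 175, or 87.5 per arm. The difference is 20 points. The control rate is not given, so the rates below are assumptions.

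| Assumed control rate | One-sided 5% | Two-sided 5% |
|---|---|---|
| 14% | 93.2% | 87.9% |
| 20% | 89.8% | 82.9% |
| 25% | 87.6% | 79.7% |
| 30% | 86.0% | 77.5% |
| 40% | 84.6% | 75.8% |
| 66% | 93.2% | 87.9% |

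The stated 88% fits a one-sided test with a control rate near 25%. It would also fit a two-sided test with a control rate near 14% or 66%.

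**The case against.** The strongest objection is that 70% is not the trial's power. The 95 per arm is a minimum number of evaluable patients, and the plan recruits 300 with intention-to-treat as the main analysis. Other Instruments lets providers as well as patients update the quality indicators, so a patient who stops using the app need not lack the primary outcome. If nearly all 300 are analysed, two-sided power is up to 88% and the promise is kept. This stands in part: the shortfall depends on retention. But the plan itself assumes 30% attrition, and at 105 per arm two-sided power is 74%.

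A reader might infer that the 88% for QOL holds only for a one-sided test. The article does not support that. It labels the figure one-sided, but without a control rate the number alone cannot exclude a two-sided calculation.

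A reader might also infer that the trial will be judged at a one-sided 5% level, doubling the conventional 2.5% chance of a false claim for the app. The Overview describes no one-sided analysis. That outcome is possible while both statements stand, but it is not what the article says will be done. The better-supported consequence is misstated planning power.

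Finally, a one-sided test can be legitimate. It cannot stand beside a two-tailed promise in the same section.

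**Conclusion.** The point holds. One section states two incompatible significance levels, and the sample size follows the more lenient one. At 95 evaluable per arm, two-sided power for 85% versus 70% is 70.0%, about 10 points below the level promised. Under the plan's 30% attrition it is about 66% with 250 enrolled and 74% with 300. It reaches 80% only with at least 121 analysed per arm.

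These figures rest on the article's own rates, 1:1 allocation and an uncorrected chi-square test; a continuity correction would lower the two-sided power at 95 per arm to 63.6%. They concern the proportion meeting all indicators, which the sample-size section calls primary but Outcome Measures lists as secondary, the listed primary being the number met. The restated power applies to the former only. For QOL, the level needs correcting, but the size of the loss cannot be fixed without a control rate.

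**What to change.** 1. State two-sided 5% as the single significance level for primary and secondary tests, in line with the section's opening paragraph, and delete both one-sided statements.
2. Amend the opening power sentence so that it no longer promises more than 80%. Give about 74% for 85% versus 70% with 105 evaluable per arm, or 80% for a difference of about 16 points. Show the dependence on retention: 66% at 87.5 per arm, 80% at 121, 88% at 150.
3. For QOL, state the assumed control rate of patients reaching the minimal clinically important difference and recompute at two-sided 5%. As an illustration only, control rates of 20% to 40% give about 76% to 83% at 87.5 per arm.

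The cost is wording and a less favourable stated power; no extra patients are required. If the sponsor prefers to keep 80% for a 15-point difference at 30% attrition, enrolment would be 2 × 121 / 0.70 = 346, which is 46 above the present target.
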